#### Secondary outcome measures

Secondary outcomes will be measured on choice predisposition, value, preparation for decision making of the patients, acceptability of the tool, and feasibility of DA delivery as part of usual clinical practice.

Acceptability of the decision aid among patients, value score related to each surgical option, and preparation for decision making score will be summarized and described. Preferred choice will be measured before and after the DA administration and the proportion of people with change in preference will be described. Feasibility of DA delivery will be described as manifest through mean time spent on the pre-decision aid questionnaire and the impact on subsequent length of surgical consent visit.

Data will be entered and stored in a database on a password-protected computer on site. Data checking will be performed to identify duplications and missing data. Strategies including case-wise deletion, variable deletion, and imputation will be considered to handle missing data. Analysis will be done through SAS 9.2 statistical software.

### Ethics approval

This project has been approved by the Ottawa Health Science Network Research Ethics Board.

### Part 2: survey of surgeons and nursing staff

Research question: What are the perceived facilitators and barriers influencing the implementation of the rectal cancer decision aid according to the healthcare providers?

### Study design

A web-based survey will be guided by the Knowledge to Action Framework [33] using the survey implementation method proposed by Couper on Internet survey design [48]. Knowledge to Action Cycle [34] states that barriers to knowledge use are important to determine prior to implementation of knowledge translation tools such as patient decision aids in clinical practice [33]. An internet survey is the most feasible option to reach the broad target population of all Canadian colorectal surgeons working with rectal cancer patients. Consistent with other survey methodologists, Couper suggests that survey implementation should include three stages in pre-notification, invitation to survey, and follow-up. The current study will include all three stages.

### Sampling frame

Colorectal surgeons in Canada can be identified by membership with the Canadian Society of Colon and Rectal Surgeons (CSCRS). This organization has been contacted and a list of members’ updated emails are maintained and accessible. There are an estimated 114 surgeons registered with CSCRS. Eligible surgeons working specifically with rectal cancer patients will be identified by the first question in the online survey.

### Procedure

An email will be sent to all surgeons in the directory. Publicly available member lists will be compared to eliminate potential duplicates. An online survey will be created via Fluid Surveys. To maximize the response rate, the survey implementation will follow recommendations of Couper [48], consisting of a pre-notification email, a personalized email invitation to participate with the decision aid attached and a link to the online survey, a reminder email will be sent on days three and six following the invitation email. A final email reminder to non-responders will be sent to further encourage response on day ten.

### Instrument

A single survey tool modified from the Facilitators and Barriers Survey by Graham et al. will be used for physicians [49]. The 41 item survey will be divided into five main areas: 1) development of the decision aid; 2) content and format of the decision aid; 3) decision aid and meeting patients’ needs; 4) physicians’ clinical practice; 5) implementation. All questions will be rated on a 5-point scale from 1 (strongly agree) to 5 (strongly disagree). There are two questions asking surgeons how likely they are to use the decision aid, rated as “not at all” to “very likely”. Two questions will explore the additional facilitators and barriers not mentioned in the survey. Two questions will explore program specific adaptation and further comments. This survey tool was first used in a study of 270 physicians in three different specialties and later modified for two subsequent studies of nurses. Using principal component analysis with Verimax rotation, Graham et al. showed factorial validity with survey items loaded on four components including quality and value for patients, value for physicians, decision aid content, and implementation issues [49]. The same survey tool was then adapted and used in studies to assess factors influencing nurses’ use of decision aid in a primary care call center [50] and an Australian cancer call center [51].

### Outcomes

The response rate will be determined. Common barriers and facilitators to the implementation of the decision aid will be identified. The primary outcome is intention to implement the decision aid. The response distribution will be analysed, and we will identify factors affecting the intention to implement the decision aid.

### Statistical analysis

Data will be captured by the online survey software and downloaded to the study database. Response rate will be determined based on the total number of completed, partially completed, refusals and breakoffs, noncontact (failed to deliver), and unknown eligibility. Ineligibility will be determined by the first question on the survey asking respondents to identify whether they are surgeons working with rectal cancer patients. Non-response rate will be reported. Descriptive statistics will be used to generate characteristics of survey respondents. All response distribution will be presented.

The intention question on the physicians’ likelihood of using the decision aid will be dichotomized into a binary variable with ‘likely’ and ‘very likely’ versus the rest of the responses. Intention will be subsequently used as a response variable in a logistic regression model. Principal component analysis with Verimax rotation will be performed on all items to confirm common themes and logistic regression analysis will be used to identify independent variables associated with the intention to use the decision aid. The independent variables will be components extracted from principal component analysis.

Item-missing data will be explored and addressed by casewise deletion, variable deletion, and possibly imputation, depending on its extent and nature. Respondents presenting with more than half missing values will be excluded from analysis.

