## Discussion

Shared decision making is a strategy that is being promoted across the healthcare systems in the US and Canada [52]. Currently the rectal cancer decision aid has been developed, but has not been formally evaluated. This study aims to evaluate the decision aid and explore the perceived barriers and facilitators to the implementation of the decision aid. It will help with planning strategies for designing interventions to facilitate implementation and overcome known barriers to use of the decision aid in routine clinical practice [32].

Physician/nursing/management collaboration will also be a major factor in completing the pre- and post- study. We will hold meetings with surgeons and nursing staff at the Cancer Assessment Centre to increase awareness among staff. Information sheets will be available in the rectal cancer clinics to remind the staff of inclusion & exclusion criteria of the study.

The single arm pre- and post- design of the study and the lack of control and blinding pose threat to our ability to make causal inferences. Nonetheless, important information will be obtained on how the rectal cancer DA may impact the choice and decision-making process of a patient, the acceptability of the decision tool to patients, and the feasibility of integrating this decision aid into everyday practice.

For the survey study, low survey response rate may introduce non-response bias where responders and non-responders are different. Therefore, this study will attempt to maximize response rate by obtaining accurate email addresses, using a simple and concise questionnaire, and sending follow up reminders [48]. Response/non-response will be reported. Discussion of possible bias will be an important part of the interpretation of the findings.

The implementation of the decision aid could lead to more evidence based knowledge dissemination related to rectal cancer and the surgical choices, less uncertainty related to decisions, and ultimately decisions more congruent with patients’ values. To our knowledge this is the first study designed to evaluate a decision aid in the field of colorectal oncology. The data collected from this study could lead to more definitive large scale studies on the surgical decision aid in the future.

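### Part 2 cuts its graded primary outcome, intention, to two classes for its only regression and so gives up roughly 20–44% of the information collected

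*Protocol article*

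**What the plan says.** The Part 2 Outcomes section states: "The primary outcome is intention to implement the decision aid". The Instrument section describes how it is collected: "There are two questions asking surgeons how likely they are to use the decision aid, rated as “not at all” to “very likely". It gives the end anchors only, not the number of levels for these two items; the other items use five points.

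The Part 2 Statistical analysis section says that the surgeons' "likelihood of using the decision aid will be dichotomized into a binary variable", with the top two answers set against the rest, and continues: "Intention will be subsequently used as a response variable in a logistic regression model". The predictors are the components extracted by principal component analysis. The same section promises to present all response distributions, but it plans no ordinal or continuous analysis of intention and gives no reason for the cut.

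On the number of respondents, the Sampling frame section says: "There are an estimated 114 surgeons registered with CSCRS". It adds: "Eligible surgeons working specifically with rectal cancer patients will be identified by the first question in the online survey". No expected response rate is given; the Discussion acknowledges only that a "low survey response rate may introduce non-response bias where responders and non-responders are different". Respondents with more than half of their values missing are also dropped.

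**The concern.** The split treats 'likely' and 'very likely' as the same answer, and everything from the bottom anchor up to just below 'likely' as the same answer. The ordering within each side, which the survey has already collected, plays no part in the one analysis meant to identify what drives intention.

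The frame is about 114 society members and can realistically only shrink, through the eligibility question, non-response and the exclusion of mostly incomplete questionnaires. Recruiting longer, as Part 1 does until it reaches its target, is not an option in a membership list. What is at stake is the chance of detecting a component that is truly related to intention.

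**Working it through.** **Figures in the plan.** Part 2 states no sample size, power or effect size, so there is no figure to reproduce. The only stated calculation belongs to Part 1 (paired t-test, difference 0.3, SD 0.6, alpha 0.05, power 0.80). It reproduces at n = 34 (power 0.808), and 34/0.9 = 37.8, which rounds up to 38. It has no bearing on the survey.

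**Inputs.** From the article: a frame of about 114, the cut at the top two levels, binary logistic regression, and predictors that are principal components. Assumed, because the article does not give them: four or five levels, the distributions below, four components (the number reported for the earlier validation in the Instrument section), two-sided alpha 0.05, an odds ratio of 1.5 to 2.0 per SD of a component, and 40 to 114 respondents.

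**Information per respondent.** For a log odds ratio under proportional odds, the graded answer carries (1 − Σpₖ³)/3, where pₖ is the share in level k. The binary answer carries p(1 − p), where p is the share at 'likely' or above. Their ratio is the relative efficiency of the cut.

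- Four equal levels: graded (1 − 4 × 0.015625)/3 = 0.3125; binary 0.50 × 0.50 = 0.25; ratio 0.80.
- Five equal levels: graded (1 − 5 × 0.008)/3 = 0.32; binary 0.40 × 0.60 = 0.24; ratio 0.75.
- 5/10/20/40/25%: Σpₖ³ = 0.08875; graded 0.30375; binary 0.65 × 0.35 = 0.2275; ratio 0.75.
- 80% at 'likely' or above: binary 0.80 × 0.20 = 0.16; ratio 0.556. A split that gives this is 2/5/13/45/35%: Σpₖ³ = 0.1363, graded 0.2879, and 0.16/0.2879 = 0.556.
- Other distributions: ratio 0.70 (four levels, 70% at 'likely' or above), 0.69 (30%) and 0.59 (25%).

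The ratio thus runs from 0.556 to 0.80, a loss of 20% to 44%. Applied to the full frame, 114 × 0.80 = 91 and 114 × 0.556 = 63.

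**Power, large-sample approximation.** Power = Φ(√(N × information) × ln OR − 1.96). For N = 57, OR 1.8 and five equal levels:

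- Graded: √(57 × 0.32) × 0.588 − 1.96 = 0.55, power 0.71.
- Binary: √(57 × 0.24) × 0.588 − 1.96 = 0.21, power 0.58.

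The same formula gives:

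| N | OR | Distribution | Graded | Binary |
|---|---|---|---|---|
| 114 | 1.8 | five equal levels | 0.94 | 0.87 |
| 80 | 1.8 | five equal levels | 0.84 | 0.73 |
| 40 | 1.8 | five equal levels | 0.56 | 0.44 |
| 114 | 1.8 | 80% likely or above | 0.92 | 0.71 |
| 57 | 1.8 | 80% likely or above | 0.66 | 0.43 |
| 114 | 2.0 | five equal levels | 0.99 | 0.95 |
| 114 | 2.0 | 80% likely or above | 0.98 | 0.84 |

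Across all the distributions at OR 1.8, the loss is 6–21 points at N = 114 and 10–23 points at N = 57.

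**Simulation with four components, likelihood-ratio tests (400 runs per cell, OR 1.8).** Graded versus binary power with five equal levels was 0.92 versus 0.81 at N = 114 and 0.68 versus 0.55 at N = 57. With 5/10/20/40/25% it was 0.90 versus 0.80 and 0.67 versus 0.53. Type I error was 0.05 to 0.07 for both models.

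**Simulation from a latent normal, correlation 0.42, four predictors, several four- and five-level distributions (250 runs per cell).** Likelihood-ratio power gaps were about 7–27 points for n = 46–91, largest for lopsided answers. With 250 runs, the Monte Carlo standard error of one power estimate is at most √(0.25/250) = 0.03, so the ends of that range are approximate.

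**The case against.** The strongest reply is that Part 2 is exploratory and makes no power claim that could fail. The cut is pre-specified, it separates likely adopters from the others in a way that suits implementation planning, and the full distribution will be shown. All of that is true. It rules out a data-driven cut and protects the description, but it does not restore information to the regression, which is the only inferential analysis.

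A second reply is that the size of the loss depends on the test and on assumptions. This stands in part. For a 10/20/20/30/20% distribution (an exact 50/50 cut) at n = 46, Wald tests gave binary versus graded power of 0.59 versus 0.79, while likelihood-ratio tests gave 0.67 versus 0.80. The Wald test therefore exaggerates the gap in small binary models, which is why the range relied on here uses likelihood-ratio tests. The gap narrows but does not vanish.

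Three stronger readings are tempting and should not be adopted:

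- A reader might infer that the effective sample shrinks to the smaller class. It does not: binary information scales with N × p(1 − p). The smaller class matters for events per predictor. With four predictors that is about 6–14 at N = 114 and 3–7 at N = 57.
- A reader might infer that the binary model could support only one or two predictors. That needs a lopsided split and a low response, and the article gives neither a distribution nor a response rate.
- A reader might infer that the survey cannot afford the cut at all. With all 114 responding and an odds ratio of 2.0, binary power is still about 0.84–0.96.

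**Conclusion.** The point holds as an avoidable loss of efficiency on the primary outcome of Part 2. It is neither an error nor a contradiction in the analysis. Under proportional odds the cut discards roughly 20–44% of the information, and likelihood-ratio power drops by roughly 7–27 points at 46–91 respondents for a latent correlation of about 0.42.

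The size rests on assumptions the article does not supply: the number of levels, the spread of answers, the response, the effect and proportional odds itself. If proportional odds holds, the direction does not depend on the others, except that nothing is lost if answers fall in only two levels on opposite sides of the cut. The 114 is itself an estimate, so it is an approximate ceiling.

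One related ambiguity should be settled at the same time. The Instrument section has two likelihood-of-use questions, while the Statistical analysis section speaks of a single intention question, so which one is modelled is not fixed.

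**What to change.** In the Part 2 Statistical analysis section:

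1. Name which of the two likelihood questions is the primary outcome, and state its levels.
2. Make the main model a proportional-odds logistic regression of the full intention scale on the planned principal components, with likelihood-ratio tests. The components stay as planned; replacing them with predefined subscale scores would be a separate change and is not needed here.
3. State in advance a rule, with a numerical threshold, for merging sparse adjacent levels, so that no data-driven collapsing enters.
4. Report the proportion answering 'likely' or 'very likely' with a 95% CI as the headline description, and keep the pre-specified binary logistic model as a sensitivity analysis.
5. Examine proportional odds by comparing estimates across the possible cut-points. The single binary model cannot do this alone, and a violation will be hard to detect at this sample size.

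The cost is a few sentences of analysis wording, with no new data. The real downside is reliance on proportional odds.

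### Part 2 does not exclude the two likelihood-of-use questions from the component analysis that supplies the predictors of intention, and does not say which of the two is the outcome

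*Protocol article*

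**What the plan says.** Three statements in the Part 2 Statistical analysis section belong together. On the outcome: "Intention will be subsequently used as a response variable in a logistic regression model". On the items analysed: "Principal component analysis with Verimax rotation will be performed on all items to confirm common themes". On the predictors: "The independent variables will be components extracted from principal component analysis". No item is excluded from the component analysis.

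The Instrument section describes the tool: "The 41 item survey will be divided into five main areas", and "All questions will be rated on a 5-point scale from 1 (strongly agree) to 5 (strongly disagree". It then adds that "There are two questions asking surgeons how likely they are to use the decision aid", on a scale from not at all to very likely. Two further questions ask about other facilitators and barriers, and two about program adaptation and comments. The section does not say whether these six are among the 41.

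The Statistical analysis section speaks of one intention question, in the singular; the Instrument section lists two.

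**The concern.** A regression meant to show which opinions go with intention is informative only if the predictors are measured separately from intention. If a likelihood-of-use question helps to build the component scores, a component can be associated with intention because it contains intention. Removing only the outcome question would not fully cure this, because the second question asks nearly the same thing.

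Intention is the primary outcome of Part 2, and identifying what affects it is a stated aim (Part 2, Outcomes). The Background says the results will guide the choice and tailoring of implementation strategies. A component driven by the intention questions would be reported as a factor while saying nothing about barriers.

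**Working it through.** Part 2 states no sample size, power or error rate, so there is no figure to reproduce. The check is whether the literal rule distorts the regression, and by how much.

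**Mechanism.** A component score is a weighted sum of the standardised items, S = Σ w_j z_j. Let y be dichotomised intention. Then

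Cov(S, y) = Σ(opinion items) w_j Cov(z_j, y) + w_a Cov(z_a, y) + w_b Cov(z_b, y),

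where a is the question used as the outcome and b is its twin. If no opinion item is related to intention, the first sum is zero on average. The other two terms are not zero unless the weights are, because z_a is y before dichotomisation and z_b is correlated with it. Dropping both questions removes both terms. Dropping only a leaves the term in b.

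**Inputs from the document.** 41 items; two likelihood-of-use questions; five-level items; four components reported earlier for the source tool (Instrument). The upper limit on respondents comes from the Sampling frame section: "There are an estimated 114 surgeons registered with CSCRS".

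**Assumed inputs.** Intention unrelated to every opinion item; four true components; 400 simulated surveys per case; sample sizes from 57 (114 × 0.5) to 114. Two sets were run:

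- Set A: 39 opinion items (41 − 2), loading 0.7, correlation 0.7 between the two intention questions before five-level coding, n = 57, 80 and 114.
- Set B: 37 opinion items, loading 0.6. The correlation assumed between the two intention questions is not available to report, so this set is indicative only.

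If the six extra questions are inside the 41, there are 41 − 6 = 35 agree/disagree items; if outside, 41. Both 37 and 39 lie between these.

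**Procedure.** Principal components with varimax rotation, then a logistic regression of intention (likely or very likely against the rest) on the component scores, with an overall likelihood-ratio test at 0.05.

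**Share of surveys with a significant test although no association exists:**

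| Set | Components kept | Both intention questions in | Twin only in | Both out |
|---|---|---|---|---|
| A | 4 | 23.75% to 26.25% | not run | 5.5% to 6.75% |
| A | 5 | 99.5% to 100% | not run | 6.0% to 7.5% |
| B | 4 | 42% to 50% | 11% to 14% | 4% to 8% |
| B | 5 | 99% to 100% | 34% to 59% | 4% to 8% |

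The simulation standard error at a true 5% is √(0.05 × 0.95 / 400) = 1.1 percentage points. The figures with both questions out are therefore close to nominal; the highest in Set A, 7.5%, is about 2.3 standard errors above 5%.

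In Set A with five components, the mean in-sample area under the ROC curve was 0.92 to 0.95 with the intention questions in, against 0.62 to 0.68 with them out. The fifth component is then largely the two intention questions themselves.

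**The case against.** The strongest reply is that the authors never meant the intention questions to be in the component analysis. Several points in the document favour this:

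- The Instrument section lists them apart from the five agree/disagree areas and on a different scale.
- That section says all questions use the agree/disagree scale and then describes questions that do not, so the authors do not use the word all strictly.
- A comments question cannot enter a component analysis, so the phrase about all items cannot cover every question.
- The Statistical analysis section makes intention the response before it mentions components.
- The earlier analysis found that "survey items loaded on four components including quality and value for patients, value for physicians, decision aid content, and implementation issues"; none of the four is named as intention.

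This stands as far as it goes. A reader might infer that the plan does place the outcome among its own predictors; the document does not say so. It does not rule it out either. The comments question stays out because it cannot be scored, whereas the likelihood-of-use questions are ordinal ratings that can enter, and a different scale is no obstacle when correlations are analysed. Even an analyst who drops the outcome question has no instruction about its twin.

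It is also fair to say that the sizes depend on assumptions. The four-component figure roughly halves between the two sets, and the near-certain rejection needs a fifth component that the document does not plan.

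Finally, the descriptive results of Part 2, including the distribution of intention itself, do not depend on this step.

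**Conclusion.** The point holds as an ambiguity with a harmful literal reading. The plan sets the component analysis without excluding the two likelihood-of-use questions, makes the components the predictors of intention, and leaves open which question is the outcome. If both questions enter, false association rises from about 4% to 8% to about 24% to 50% with four components, and to nearly 100% if a fifth forms from the intention questions. The direction follows from the algebra. The sizes rest on assumed loadings, an assumed correlation between the two questions, and the number of components kept.

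A reader might go further and infer that re-extracting components from so few surgeons is itself an error, and that fixed scores from the earlier four components must replace it. The document does not support that as a required correction:

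- No rule for how many components to keep is stated, and an article may leave that to the full plan. A simulated 10 to 12 components requires assuming the eigenvalue-above-one rule.
- With an assumed 50% response and 40% in the smaller class there are 114 × 0.5 × 0.4 = 22.8, or about 23, events. That is about 2 per component with 10 to 12 components, but 23 / 4, about 6, with the four reported earlier.
- A loss of over half the respondents to casewise deletion (0.98^41 = 0.44 kept) assumes 2% missing per item and treats as the plan one of several options listed.
- Fixed scores need item loadings that are not shown, for a tool that has since been modified.

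**What to change.** In the Part 2 Statistical analysis section, replace the reference to all items with the agree/disagree barrier and facilitator items, and state that both likelihood-of-use questions and the open questions are excluded. Name which of the two likelihood-of-use questions is dichotomised as the regression outcome, and say that the other is only described. In the Instrument section, say whether the six additional questions are among the 41.

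This is a change of wording, best made before the responses are seen. It needs no new data and no change to the survey, and the planned component analysis and regression otherwise stay as they are. Scores based on the earlier four-component structure could be added as a sensitivity analysis if the loadings are available, but this is optional.

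### The survey PCA is set to run on all items without excluding the two likelihood-of-use questions, so the predictors of intention could contain the outcome

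*Protocol article*

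**What the plan says.** All references are to Part 2 of the protocol article.

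- **Instrument.** One survey tool is described: "The 41 item survey will be divided into five main areas". Its main scale follows: "All questions will be rated on a 5-point scale from 1 (strongly agree) to 5 (strongly disagree". The next sentence adds that "There are two questions asking surgeons how likely they are to use the decision aid", on a separate scale running up to very likely. Two further questions are exploratory ("Two questions will explore the additional facilitators and barriers not mentioned in the survey"), and two more cover local adaptation and comments. The section does not say whether these six are counted among the 41.
- **Statistical analysis, response.** "The intention question on the physicians’ likelihood of using the decision aid will be dichotomized into a binary variable", and then "Intention will be subsequently used as a response variable in a logistic regression model". Intention is in the singular.
- **Statistical analysis, predictors.** "Principal component analysis with Verimax rotation will be performed on all items to confirm common themes". Then: "The independent variables will be components extracted from principal component analysis". No item is listed as left out.
- **Outcomes.** Intention to implement the aid is the primary outcome of the survey, and the factors affecting it are to be identified.

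**The concern.** A component score is a weighted sum of the items entered. If the intention question is one of those items, part of the outcome sits on both sides of the logistic model, and some association is built in whatever surgeons think of the aid. Removing only the question used as the response does not fully cure this, because the other likelihood-of-use question asks nearly the same thing and would carry much of the same signal.

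The regression is the planned route to the factors behind the survey's primary outcome, and the Discussion says the study will inform strategies to overcome barriers. A theme could be reported as a barrier or facilitator because it shares a component with the outcome.

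**Working it through.** **No figure to reproduce.** Part 2 states no sample size, power or significance level. The check is therefore a reading of the text, followed by an illustration of what the literal reading would cost.

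**Reading the sections together.**
1. The PCA input is all items, undefined (Statistical analysis).
2. The tool contains two rated likelihood-of-use questions (Instrument).
3. The predictors are the components from that PCA, and the response is one of the two questions (Statistical analysis).
4. No sentence removes either question at step 1. Literal reading: both enter. Half-literal reading: the response is removed and the other stays. Narrow reading: only agree/disagree items enter.

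**Illustration under the null.** Three sets of simulated surveys were used, with intention unrelated to every barrier item. Each ran PCA with varimax rotation, logistic regression of intention on the components, and an overall likelihood-ratio test at 5%. Item structure and correlations are assumptions. From the document come only the 41 items and the frame of 114 surgeons, which caps the number of respondents. If all six extra questions are among the 41, the rated items number 41 − 2 − 2 − 2 = 35. If only the likelihood questions are taken off, 41 − 2 = 39.

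| Set | Assumptions | Kept | Both in | Second only in | Both out |
|---|---|---|---|---|---|
| A | 35 items, 4 or 5 themes, loading 0.7, intention pair correlated 0.7, n = 60–80 | 4 | 26–29% | 10–11% | 5–8% |
| A | same | 5 | 100% (4 themes); about 50% (5 themes) | 54–70% | 5–8% |
| A | same, n = 60 | eigenvalue above 1 | 100% | about 80% | about 10% |
| B | 39 items, 4 themes, loading 0.65, pair correlated 0.6, N = 40, 57, 80, 114 | 4 | 23–34% | not run | 4–10% |
| B | same | 5 | 85–100% | not run | 4–10% |
| C | 35 items, 4 themes, n = 60–80 | 4 | 28–29% | 8–14% | 5–9% |
| C | same | 5 | 100% | 49–61% | 5–9% |

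The both-out ranges for A, B and C cover four and five kept together. The 10% in set B is N = 40 with five kept.

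**Simulation error.** With the 300 surveys per setting of set B, the standard error is √(0.05 × 0.95 / 300) = 1.3 percentage points near 5%, and √(0.30 × 0.70 / 300) = 2.6 points near 30%. The gap between both in and both out is not noise.

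**Why the number of components kept matters so much.** In set A with four themes, each theme has 35/4 = 8.75 items on average. Before any loss from categorizing answers, its population eigenvalue is 1 + 7.75 × 0.7² = 4.80. The intention pair, unrelated to the rest, has 1 + 0.7 = 1.70, and the remaining theme directions have 1 − 0.7² = 0.51. In set B the same sums give 1 + 8.75 × 0.65² = 4.70 for a theme (39/4 = 9.75 items) and 1 + 0.6 = 1.60 for the pair. The pair therefore ranks fifth. Keep five and it tends to get a component of its own that predicts intention almost by definition; set B gave a mean McFadden R² of about 0.41–0.51 there. Keep four and the pair only leaks into components dominated by the themes, so the inflation is smaller.

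**The case against.** The strongest reply is that the document's own usage points to the narrow reading. In the Instrument section, the statement that all questions use the agree/disagree scale cannot cover the likelihood questions, which are introduced immediately afterwards with a different scale. All items in the Statistical analysis section can be read the same way. This stands. A reader might infer that the plan commits to a circular regression, but the documents do not say that the two questions enter the PCA.

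Other points on that side:

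- *Some narrowing is needed anyway, since comment questions and the eligibility screener cannot sensibly enter a PCA.* True, but free-text answers drop out mechanically. The likelihood questions are rated, and a different response scale does not keep them out of a correlation-matrix PCA.
- *Intention is assigned as the response before the PCA is mentioned, and none of the four components found earlier with this tool is named as intention.* This supports the narrow reading but protects only one of the two questions. The article does not say which items entered that earlier analysis.
- *A condensed article may leave item lists to a fuller document.* Fair for a missing list. Here the article does state the input set, in words too wide for its purpose.
- *The simulations rest on assumptions, and an intention-only component would be visible in the loadings.* Both stand. The figures near 100% largely describe that visible case, so the four-kept figures are nearer to the harm described. Even those come from an overall test; how often a single barrier theme would be falsely flagged was not estimated.

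**Conclusion.** The point holds as a badly worded rule of moderate severity, not as an established circular analysis. The PCA input is stated too broadly, the two likelihood-of-use questions are not excluded, and the response is one unnamed question of the two. One available reading of the sentence gives an invalid model and another gives a valid one.

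If the literal reading were followed, the illustrative null rate of overall significance would be about 23–34% with four themes and four components kept, and 85–100% with five kept. With only the second question left in, it would be about 8–14% and 49–70%. With both out, it is about 4–10%. The direction follows from how the components are built. The size depends on the assumed items, themes and correlations, the number of respondents and the number of components kept; five themes with five kept, for example, gave about 50% with both questions in.

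**What to change.** In the Part 2 Statistical analysis section:

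1. Replace the PCA on all items with a PCA on the agree/disagree barrier and facilitator items, excluding both likelihood-of-use questions.
2. State that only components built from those items are predictors in the logistic model.
3. State which of the two likelihood-of-use questions is dichotomized as the response.

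The cost is a sentence or two of text, with no change to the questionnaire, data collection, sample or staff. If the narrow reading was always intended, the planned analysis does not change, apart from naming the response question.
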